### Study oversight

#### Centralized IRB and Data and Safety Monitoring Board (DSMB)

This study utilizes a centralized IRB such that the study sites have ceded review to the Mass General Brigham IRB (the “reviewing IRB”). The DSMB, which meets via teleconference every 6 months, is responsible for ongoing monitoring of the trial with the purpose of ensuring study safety and integrity. The DSMB members, as well as an internal safety monitor with expertise in clinical trials of depression, review any serious adverse events that are possibly, probably, or definitely related to study participation. The DSMB prepares an annual report of its findings regarding safety and quality with any recommendations to improve patient safety, protocol adherence, or data quality. This report is sent to the Mass General Brigham IRB.

#### Study committees

Our study committees are described in Table 4. We highlight here the role of our Advisory Board. Study partners (i.e., members of the Advisory Board) are involved in all aspects of study design, implementation, and dissemination of study findings. The Advisory Board meets at least quarterly, but also more frequently as needed (e.g., monthly prior to launching the study). Our partners hold expertise and experience of relevance to the current proposal, and include individuals with lived experience of depression, caregivers for an individual(s) with lived experience of depression, yoga instructors, mental health providers, payors (e.g., representatives from insurance companies), experts in clinical trials of depression, diversity, inclusion, and equity experts, and representatives from advocacy organizations. The Advisory Board discusses key study decisions and makes recommendations to the Steering Committee, which then provides direction and feedback to the rest of the study committees. For example, some partners are experts in patient experience and retention in clinical research and they can offer specific guidance on improving recruitment strategies. Partners also offer guidance on the format and content of outreach efforts to aid recruitment of individuals across racial/ethnic backgrounds, education, and income levels and to keep participants engaged in completing the study interventions and assessments.

**Table 4 pone.0315506.t004:** Description of study committees.

*Committee*	*Description*
Steering Committee	Responsibilities: Oversee all study committees and implementation of study procedures at all sites. Provide input on key scientific issues that arise during study implementation, operation, and data analysis phases. Members: Study PIs, site PIs and co-Is, Safety Officer, site research managers, study partners. Frequency of meetings: Biweekly (every other week).
Study Operations Committee	Responsibilities: Write manual of procedures; support implementation of study operations across sites. Review adverse events, protocol deviations, participant safety, and recruitment and retention. Members: Study PIs, site research staff Frequency of meetings: Weekly.
Communications Committee	Responsibilities: Oversee creation of study recruitment and engagement materials. During study operation, discuss ways to increase recruitment and engagement (i.e., ways to distribute social media advertisements, advertisement language) with Advisory Board, study staff, site PIs, and study PIs. Collaborate with Data Committee and Steering Committee on dissemination of results. Members: Co-Is, communication manager, one staff member from each site, social media consultant, and study partners. Frequency of meetings: Biweekly during study start-up, and then as needed once study is running.
Data Committee	Responsibilities: Oversee database creation and management, ongoing data integrity checks, and data analysis and interpretation. Members: Data managers, statisticians, study PIs, staff from each site who regularly use the REDCap database. Frequency of meetings: Biweekly.
Yoga Intervention Committee	Responsibilities: Oversee training, implementation, and fidelity ratings of yoga intervention. Provide supervision to yoga teachers. Members: Yoga consultants/fidelity raters, a PI, co-I, study partners with expertise in YIs, and study staff who help to host yoga classes. Frequency of meetings: Monthly during study start-up, then bimonthly.
Behavioral Activation Intervention Committee	Responsibilities: Oversee training, implementation, and fidelity ratings of psychotherapy sessions. Host BA therapist supervision meetings. Members: Co-Is and study partners with expertise in BA. Frequency of meetings: Biweekly.
Data Safety and Monitoring Board (DSMB)	Responsibilities: Review adverse events, protocol deviations, data integrity, recruitment and retention, and participant demographics. Members: Four doctoral-level individuals not otherwise involved in this study and independent from PIs and co-Is. Frequency of meetings: Twice per year.
Advisory Board	Responsibilities: Advise Steering Committee on design and implementation of the study and dissemination of study results. Members: Study partners, including people with lived experience, caregivers, yoga instructors, mental health providers, payors, patient advocates, and people with expertise in other relevant areas (e.g., study design, dissemination). Two members of the Steering Committee attend. Meeting frequency: Quarterly or more often as needed.

### Safety procedures

#### Procedures for monitoring adverse events

Adverse events (AEs) as defined by OHRP [100] are assessed in two ways: 1) the participant mentions an experience during an intervention session that the instructor/clinician records as a potential AE; or 2) the participant self-reports a potential AE (e.g., a scheduled surgery, muscle soreness) via a survey question. All potential AEs are reviewed by the research team and coded for severity, relatedness, and expectedness. AEs are discussed on the weekly Internal Study Operations and Safety committee meeting with staff from all study sites. Serious adverse events (SAEs) are reviewed immediately (within 24 hours) by the study PIs and/or the internal safety monitor and reported promptly to the IRB, DSMB, and PCORI (if required). All SAEs and related AEs are shared with the IRB, DSMB, and PCORI in annual progress reports.

#### Procedures for monitoring suicidal ideation

Suicidal ideation and behavior are assessed every 6 weeks via the CSSRS Screen Version–Recent SR in REDCap. If a participant’s scores indicate suicidal ideation or suicidal behavior in the past 3 months (i.e., positive response to items 3, 4, 5, or 6), the participant receives an automated REDCap message with a) information about the National Suicide Prevention Lifeline (988) and associated website (the Lifeline is a 24/7 hotline that provides help for those at risk for self-harm), b) encouragement to reach out to a local healthcare provider, and c) a telephone number for study staff who can connect them to a study clinician. If a participant specifically endorses thinking about a method for suicide, reports an intention to act, reports preparatory behaviors, or reports an attempt in the past 3 months, REDCap provides an additional message to the participant informing them that a study clinician will outreach by telephone within the next 24 business hours. Concurrently, an automated message is sent to the Principal Investigators and study staff informing them to reach out to the study participant. A study clinician then initiates the outreach phone call, conducts a suicide risk assessment, and offers support/resources as needed. We use similar procedures if a person verbally reports suicide ideation to study staff outside the context of an assessment. That is, study staff will remind the participant about 988 as well as contact the covering clinician who will assist with an appropriate follow-up plan which may include a risk assessment with the participant. If the participant is at immediate risk, study staff will call 911 to send help to the participant’s address prior to calling the covering clinician. If a randomized participant requires a higher level of care (e.g., additional outpatient services, inpatient or partial hospitalization), they may remain in the study if they wish and may or may not continue with the study interventions depending on what is determined to be clinically appropriate by the participant and their providers. All additional services will be tracked as part of study assessments.

## Design considerations for a pragmatic effectiveness trial

Given existing research supporting the efficacy of yoga interventions and BA for depression, we determined that a pragmatic, effectiveness clinical trial was the next step in understanding how yoga interventions might have an impact on depression in the community. Therefore, we made several study design decisions to reflect a pragmatic, effectiveness trial [101]. For example, we made eligibility criteria as broad as possible, including people who may have bipolar disorder or who are taking medications for depression, and we required that participants have elevated depression symptoms but not a diagnosis of major depression for participation. The large sample size should increase the chances that study groups are ultimately balanced on these key variables.

Second, we selected BA therapists who are engaged in clinical practice (i.e., not research therapists) and have a wide range and amount of prior experience and training in CBT or BA approaches. Moreover, the BA therapists bill study participants’ insurance for participants who have adequate insurance to mirror real-world activity. The yoga intervention is also delivered as it might be in the real world, via a telehealth synchronous class with trained yoga instructors. Also, in line with a pragmatic trial, we provide interventions as they are typically delivered in the community: individually for BA and in a group format for yoga (i.e., typically 5–10 people per class). Finally, we selected a primary outcome, the PHQ-9, that is commonly used in clinical practice to assess improvement in depression symptoms.

As a result of this pragmatic study design, there are some key differences in the delivery of the two study interventions that may ultimately have an impact on overall participant adherence or satisfaction. First, the length of time to intervention start may differ. Because this is a study, we have made significant efforts to ensure that participants can start BA within 1–2 weeks of randomization; however, for scheduling and other reasons, this timing may not always occur. A participant can always start a yoga class in their first week after randomization. Second, another key difference in the interventions is that yoga classes are offered at 4 set times each week in a group format, whereas the BA sessions are determined based on the participant and therapist schedules, which may or may not allow for flexibility in scheduling. A third difference is that the BA participants often incur a cost per session given that most insurers require a co-pay for each BA session whereas the YI is delivered with no costs to participants. To increase accessibility of the research, we capped the out-of-pocket cost for the BA sessions at $25 out-of-pocket per session but nonetheless, the cost may be a burden to some participants. In contrast, yoga is provided at no cost to participants given that it is often not currently covered or reimbursed by insurers and to reflect that there are opportunities for free synchronous and asynchronous online classes in the community. For example, one insurer, Blue Cross Blue Shield (BCBS) of RI, offers free classes to its members at a BCBS store. Other community organizations, such as the YMCA, offer low-cost memberships which include yoga classes. A final key difference between the yoga and the BA interventions is documentation in the medical record–yoga classes are not documented in any medical record, whereas psychotherapy, or BA, must be documented to be reimbursed. As a result of these differences, study results will reflect potential outcome differences not only based on the “pure” intervention, but the interventions as they are delivered in the real-world, including several barriers to mental health treatment (i.e., access to BA) and access to potentially helpful treatments such as yoga.

Consistent with PCORI’s goal for pragmatic clinical trials to maximize reach [50], we employ specific strategies to ensure that our procedures are accessible to a wide range of patients. For example, we tailor recruitment materials and interventions for Spanish-speaking individuals. Participants have the option to engage in BA in Spanish with a Spanish-speaking therapist or join yoga classes with a Spanish-speaking instructor. This tailoring may help overcome language barriers that can impact enrollment of Spanish-speaking participants in clinical trials [102]. Our decision to offer the study in an entirely virtual format was chosen to further maximize accessibility and to limit barriers to study participation (i.e., cost and time associated with travel) [103]. However, we are aware that some participants may not own smartphones or computers, and so we provide tablets to participants as needed to ensure that lack of electronic device ownership is not a barrier to study entry.

This pragmatic effectiveness trial is not an implementation trial [104]. Therefore, some aspects of this study are less pragmatic and more consistent with a research study opposed to full real-world implementation. For example, we use interventionist manuals for both yoga teachers and BA therapists and have procedures to ensure treatment integrity (e.g., we provide therapist/teacher manual training, require ongoing supervision meetings, and conduct assessments of interventions delivered). We created manuals that focus on core intervention elements, but also allow some flexibility in how the interventions are delivered. Such flexibility allows interventionists to tailor the intervention to participant(s) which is more consistent with real-world practice.

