### Statistical analysis

We designed the study to determine the noninferiority of YI versus BA with a margin of 2 points on the PHQ-9 at week 24 (primary outcome). This margin was chosen as its magnitude was below established thresholds of a clinically meaningful difference on the PHQ-9 (which range from 3–5 in the literature) [52]. We arrived at this conclusion based on a few lines of reasoning. One strategy for determining a non-inferiority margin is by calculating it as one half of the mean control effect size from previous trials. A previous study of behavioral activation (BA) vs. cognitive behavioral therapy (CBT) calculated the non-inferiority margin to be 1.9 PHQ-9 points, based on a meta-analysis of previous BA trials that estimated a difference between BA and control groups of 3.8 PHQ-9 points [89]. Another study also choose a margin of 2 based on three pieces of evidence: a) a change of 2 on the PHQ-9 would correspond to a small effect size (assuming a standard deviation of 6.9), which is typically seen to be of limited clinical value; b) 2 points on the PHQ-9 represents an effect size of less than one half the expected difference between treatment and usual care; and c) psychologists using the PHQ-9 in clinical practice did not see a change of less than 2 points on the PHQ-9 to be a change that was clinically important [90]. A margin of 2 points on the PHQ-9 has also been used in prior noninferiority trials of depression treatments [91–96]. We include the non-inferiority margins for secondary outcomes in Table 3.

**Table 3 pone.0315506.t003:** Non-inferiority margins and power estimates for primary and secondary outcomes.

Outcome Type	Description	Measure	Non- inferiority Margin [Supporting Citations]	Anticipated Standard Deviation
Primary	Depressive symptoms	PHQ-9^a^	2 points^d^	7 points
Secondary	Well-being	WHO-5^b^	1.5 points [95, 109]	5 points
Secondary	Anxiety	PROMIS-29^c^	3 points [92–94]	10 points
Secondary	Sleep Disturbance	PROMIS-29^c^	3 points [92–94]	10 points

^a^ Range of possible scores = 0–27.

^b^ Range of possible scores = 0–25.

^c^ Converted to t-scores, i.e., with a mean = 50 and SD = 10.

^d^ See text for supporting citations.

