Assuming an actual mean difference of zero, a standard deviation of 7 in both arms [97, 98], and a 25% dropout rate by week 2 [33], a sample size of 518 (259 participants per arm) provides 80% power to establish the noninferiority of the YI versus BA based on a one-sided 2.5% significance level t-test against the margin of -2 points.

All statistical reporting will adhere to guidelines in the CONSORT extension for noninferiority trials [99]. The primary outcome is patient-reported depression symptom severity (PHQ-9) at week 24. The difference in the mean scores at week 24 will be estimated using a linear mixed effects model with random participant intercepts and slopes and fixed effects for intervention arm, study site, time in weeks, and intervention-by-time interaction. Natural cubic splines or categorical time regression terms will be used if mean trajectories are nonlinear. The non-inferiority of the YI will be established based on a one-sided 2.5% significance level test of the estimated difference in means against the prespecified margin of 2 points. We will also report corresponding model-based estimates with 95% confidence intervals (CIs).

Secondary outcomes including well-being (WHO-5), anxiety, and sleep (PROMIS-29) will be analyzed similarly using linear mixed models, one-sided noninferiority tests against the prespecified margins, and model-based estimates with CIs. A multiplicity correction will be used to interpret secondary outcome results to maintain an overall family-wise error rate of 5%. Exploratory outcomes will be analyzed using linear mixed models or other appropriate longitudinal regression models (e.g., quasi-poisson generalized estimating equation model for number of days of psychiatric inpatient treatment); exploratory results will emphasize model-based estimates and CIs.

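### The primary model and the 80% power assume independent participants, although yoga is taught in shared classes and BA (by inference) by shared therapists; any positive correlation makes the non-inferiority test anti-conservative, by an amount the article does not let us determine

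*Protocol article*

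**What the plan says.** The section on design considerations states that the interventions are given "individually for BA and in a group format for yoga", typically with 5–10 people in a class. It adds that "yoga classes are offered at 4 set times each week in a group format" and that a participant can join in the first week after randomization, so class membership rolls. BA therapists are practising clinicians, and the same section says that their prior experience and training vary widely.

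The Statistical analysis section specifies the primary analysis as a "linear mixed effects model with random participant intercepts and slopes", with fixed effects for arm, site, time and arm by time. No class, instructor or therapist term appears. The sensitivity analyses cover baseline imbalance and missingness only.

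The same section says that 518 participants (259 per arm) "provides 80% power to establish the noninferiority of the YI versus BA", using a one-sided 2.5% t-test against a 2-point PHQ-9 margin. No design effect or ICC is mentioned.

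**The concern.** Individual randomization makes the arms comparable at baseline. It does not keep outcomes independent once participants share a class, an instructor or a therapist. Shared delivery can induce correlation in both arms, from different sources and in clusters of different sizes.

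A model with participant-level random effects only treats between-class and between-therapist variance as if it were independent variation between people. With positive correlation, the standard error of the arm difference is then understated. In a superiority trial this inflates false claims of benefit. Here it inflates the chance of declaring a truly inferior yoga programme non-inferior, which is the claim the article hopes will inform treatment guidelines. For the same reason, the stated 80% would not hold for a t-test whose standard error allowed for the clustering.

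**Working it through.** **Inputs from the Statistical analysis section.** Margin 2 PHQ-9 points; "Assuming an actual mean difference of zero"; "a standard deviation of 7 in both arms"; "a 25% dropout rate by week 2" (only the 25% enters the arithmetic); one-sided 2.5% t-test; 259 per arm.

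**Input from the design considerations section.** Yoga class size m = 5–10 (midpoint 7.5).

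**Assumptions, not in the article.** ICC 0.01–0.05; 10 analysed patients per BA therapist where BA clustering is included. Clusters are taken as equal, fixed and exclusive.

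**Step 1: reproduce the plan's figure.**
- Normal approximation: n = 2 × 7² × (1.96 + 0.8416)² / 2² = 192.3, so 193 per arm.
- The exact t-test gives 79.9% power at 193 and 80.1% at 194, so 194 per arm are needed.
- 194 / 0.75 = 258.7, so 259 per arm and 518 in total. This matches exactly with design effect 1 in both arms.
- Baseline for what follows: 259 × 0.75 = 194.25 analysed per arm; SE = 7 × √(2/194.25) = 0.710; normal-approximation power = Φ(2/0.710 − 1.96) = 80.4%.

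**Step 2: allow for clustering.**
- Design effect in an arm: DE = 1 + (m − 1) × ICC.
- True SE = 7 × √((DE_yoga + DE_BA)/194.25), and R = true SE / 0.710.
- Error rate at a true difference equal to the margin, if clustering is ignored: 1 − Φ(1.96/R).
- Power if clustering is modelled correctly: Φ(2/true SE − 1.96).

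Worked case, yoga only, m = 7.5, ICC 0.05: DE_yoga = 1.325; SE = 7 × √(2.325/194.25) = 0.766; R = 1.078; error = 1 − Φ(1.818) = 3.4–3.5%; power = Φ(2.612 − 1.96) = 74.3%.

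| Clustering | ICC | DE yoga | DE BA | R | Error | Power |
|---|---|---|---|---|---|---|
| Yoga only, m = 5 | 0.01 | 1.040 | 1 | 1.010 | 2.6% | 79.6% |
| Yoga only, m = 10 | 0.01 | 1.090 | 1 | 1.022 | 2.8% | 78.7% |
| Yoga only, m = 5 | 0.05 | 1.200 | 1 | 1.049 | 3.1% | 76.6% |
| Yoga only, m = 10 | 0.05 | 1.450 | 1 | 1.107 | 3.8% | 72.0% |
| Yoga 7.5, BA 10 | 0.01 | 1.065 | 1.090 | 1.038 | 2.95% | 77.4% |
| Yoga 7.5, BA 10 | 0.02 | 1.130 | 1.180 | 1.075 | 3.4% | 74.5% |
| Yoga 7.5, BA 10 | 0.05 | 1.325 | 1.450 | 1.178 | 4.8% | 66.7% |

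**Step 3: dependence on how a yoga cluster is defined.** Because entry rolls, 5–10 describes who is in a class at one time, not a closed cohort.
- If the four weekly slots were the lasting clusters, m = 194.25/4 = 48.6. Yoga clustering alone at ICC 0.01 then gives R = 1.113, error 3.9% and power 71.6%.
- If a cluster were a slot within a calendar quarter, recruitment from January 2023 to May 2026 spans about 13.3 quarters, so about 53 clusters of about 3.6. Yoga clustering alone at ICC 0.05 then gives R = 1.032, error 2.9% and power 77.9%.

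The cluster definition therefore matters about as much as the ICC.

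**The case against.** **The harm is conditional.** A reader might infer that the interval is too narrow and the power overstated as a matter of fact. The article does not support that, because it reports no ICC for either arm. At ICC 0.01 with yoga clustering only, the cost is under 2 points of power and at most 0.3 points of error. The primary endpoint also falls 12 weeks after the 12-week treatment period, when class or therapist effects may have faded. This stands: the direction is certain only for a positive ICC, and the size is open.

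**The larger figures depend on an assumed caseload.** It is tempting to say that the error rate nearly doubles. The 4.8% needs both ICC 0.05 and 10 patients per therapist. The article gives neither a caseload nor the number of therapists, and that therapists are shared is itself inferred from 259 planned BA participants and a supervised therapist group. This stands as well. Shared yoga classes, by contrast, are stated outright.

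**The mixed model is not the t-test.** It uses repeated assessments and all available data, including from participants who drop out, so it may recover some power. It would therefore be too strong to say that 80% holds only at an ICC of exactly zero. But repeated measures do not restore between-cluster variance that the standard error omits.

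**Site is in the model.** Licensure ties therapists to the four states, so the site effect may absorb some between-therapist variation. It cannot absorb differences between therapists or classes within a site.

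**An article condenses, and a separate analysis plan may deal with clustering.** This would answer a complaint of mere omission. Here the article sets out the primary model's random and fixed effects and a power figure that reproduces only under independence. An analysis plan that added cluster terms would change the model as published and the basis of the power figure.

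**Conclusion.** The point holds in conditional form. Followed as written, the plan tests non-inferiority with a standard error that ignores shared delivery, and its power statement does not say that it assumes independence. Under any positive within-class, within-instructor or within-therapist correlation, the test leans towards declaring yoga non-inferior.

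On the class sizes the article gives, and with clustering in the yoga arm only, the effect runs from negligible (error 2.6–2.8%, power about 79–80% at ICC 0.01) to moderate (3.1–3.8%, 72–77% at ICC 0.05). Adding BA clustering at an assumed 10 patients per therapist moves this to 2.95% and 77% at ICC 0.01, and 4.8% and 67% at ICC 0.05. These figures illustrate a range; they do not estimate what will happen in this trial. They rest on assumed ICCs, an assumed caseload and fixed clusters. Rolling entry could make the real yoga cluster larger, or attendance across several slots could dilute it.

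**What to change.** Before outcomes are analysed:

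1. **Primary model.** Specify a partially nested model: a random effect for therapist in the BA arm only, and one for instructor or main class slot in the yoga arm only. Treat participants who attended nothing as clusters of one. State a rule for those who switch classes (main slot attended, or multiple-membership weights). Use Satterthwaite or Kenward-Roger degrees of freedom.
2. **Cluster definition.** Choose it from counts of instructors, slots and therapists, without sight of outcomes. Four slots alone would be very few levels from which to estimate a variance, so instructor, or slot within period, may serve better.
3. **Power statement.** Say that the 80% assumes no clustering, and show power for a range of ICCs such as 0.01–0.05, using the same cluster definition as the model.

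**Cost.** This is analysis wording only; it changes neither conduct nor sample size. The interval will usually be slightly wider (by the factor R above, more if there are few clusters), and the stated power less favourable. The article says that yoga attendance and BA sessions are recorded, but not that slot, instructor and therapist identity are stored in a form ready for analysis. That needs to be confirmed.
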